|                  | 
8. Translate and validate the VSS-SF scale from English to Swedish.
 
9. Investigate the frequency of benign positional paroxysmal vertigo (BPPV) after AVS at different time points and using different evaluation methods; investigate the correlation between BPPV the DHI, VSS-SF, steps and safety endpoints; and investigate the effect of treatment arm allocation on the risk for BPPV.
 
Safety objective(s): Compare the effects on the risk of falls/fractures of online vestibular rehabilitation compared with standard written instructions.
                                                                                                                                                                                                                                                                                                                                                                                                                                                                                                                                                                                                                                                                                |
| Study endpoints: | 
Primary endpoint:
The vertigo symptom scale short form (VSS-SF) score at 6 weeks after vertigo onset.
 
Secondary endpoints:
 
1. The between groups mean dizziness handicap inventory (DHI) score at 6 weeks and 3 months after vertigo onset.
 
2a. The between groups changes in timed 25-foot walk test (time duration; T25-FW) from baseline to 6 weeks and 3 months; the between group changes in kinematic and temporal parameters during walking (body sway, range of motion, gait phase durations) at 6 weeks and 3 months after vertigo onset.
 
2b. The between groups changes in body sway during the Romberg test, from baseline to 6 weeks and 3 months after vertigo onset.
 
3. The between groups changes in video head impulse test (vHIT, site-dependent) measured lateral canal VOR gain and saccades from baseline at 6 weeks and 3 months after vertigo onset.
 
4. The between groups mean vertigo symptom scale short form (VSS-SF) score at 12 months after vertigo onset; and the between group pedometer-derived number of steps walked since last visit at 6 weeks and 3 months after vertigo onset.
 
5. The between groups mean number of weekly training sessions at 6 weeks.
 |

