The motion tracking and gait data consist of sagittal and frontal plane angles and angular velocities. The planes are plotted against each other, and large deviations (quartiles or standard deviations) indicate poor balance. An artificial intelligence paradigm to analyze gait recovery will also be explored.

The VOR gain in each subject is expressed as the mean of  $\geq 5$  approved impulses for each lateral canal (right, left); on an aggregated level expressed as the median of VOR means and the changes from baseline at 6 weeks and 3 months will be compared between the study arms (affected side).

BPPV will be investigated by asking questions regarding paroxysmal motion-dependent vertigo at 6 weeks and 3 months and performing dix-hallpike and head roll testing at 3 months.

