### 9.3. Analytical procedures

Two-sided statistical tests will always be performed. The primary outcome will be analyzed using analysis of covariance (ANCOVA) adjusting for baseline measurements; known predictors of the outcome including diagnostic group, sex, age and baseline symptom intensity in order to gain precision in treatment effect estimates; and inclusion of a random effect for site to control for influence from stratified randomization. The primary endpoint results will be reported as the ANCOVA generated adjusted VSS-SF difference with 95% CI and p-value between the study arms at 6 weeks. The VSS-SF has previously been analyzed in a randomized trial assuming normality. If a clear deviation from normality is detected an ordinal logistic regression ANCOVA will be used for the primary outcome.

For secondary outcomes with repeated measurements we will use linear mixed models analysis for continuous outcome variables and binary logistic mixed effects models for binary outcome variables with random effects for individual and site. These techniques can account for repeated measures within an individual and unbalances from missing data. The intervention effect will be modelled using a time by intervention interaction term.

We will also perform statistical validation of the Swedish translation of the VSS-SF questionnaire, including analyses of reliability (test-retest reliability and internal consistency reliability) and validity; construct validity (convergent and discriminant validity) by investigating item-to-item associations between VSS-SF/VSS-SF domains and DHI; and criterion validity by correlating the domains to DHI and balance tests. For the test-retest

study, the first 100 included subjects will complete the evaluator-blinded 6-week assessments of VSS-SF twice, 48 hours apart, via telephone .

Ranked analysis of covariance (ANCOVA) will be used to evaluate intervention effects on T25-FW and VOR gain and saccades, as this method provides robust estimates even though there may be extreme outliers in skewed data. The percentage of participants with sustained improvement in VSS-SF defined as  $\geq 3$  points improvement at 6 weeks and 3 months will also be compared using binary logistic regression.

We will report crude and adjusted analyses, adjusting for baseline values of the studied outcome and the prespecified predictors sex, age, level of education, number of chronic diseases and baseline AVS etiology.

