**Table 2. Aim-specific statistical analysis plan**

| Analysis                                                                        | Subjects analyzed                         | Sample size (15% attrition is expected in power calc.) | Estimated difference based on previous results mean (SD) | Power   | Method                     |
|---------------------------------------------------------------------------------|-------------------------------------------|--------------------------------------------------------|----------------------------------------------------------|---------|----------------------------|
| Between group mean VSS-SF difference @w3, @w6, @m3, @m12                        | All participants                          | 92+92                                                  | 8.1 (7.4) vs 11.5 (9.9)                     | 90%     | ANCOVA                     |
| Between group mean EQ-5D difference until m3                                    | All participants                          | 92+92                                                  | Unknown                                                  | Unknown | Mixed models               |
| Between group mean EQ-5D difference @12m                                        | All participants                          | 92+92                                                  | Unknown                                                  | Unknown | ANCOVA                     |
| Between group mean DHI difference until m3                                      | All participants                          | 92+92                                                  | 24.4 (20.8) vs 29.2 (21.1)                  | 68%     | Mixed models               |
| Mean of means T25-FW (seconds) and timed balance tests (seconds) until m3       | All participants                          | 92+92                                                  | Unknown                                                  | Unknown | Mixed models               |
| Between group mean difference of means of vHIT gain (affected side) @w6 and @m3 | Participants at sites with access to vHIT | 50+50                                                  | 0.52 (0.24) vs 0.69 (0.25) *31                | 99%     | Ranked ANCOVA              |

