| Proportion with catch-up saccades                                               | Participants at sites with access to vHIT | 50+50                                                  | Unknown                                                  | Unknown | Binary logistic regression |

|                                                                                                |                        |       |                         |         |                            |
|------------------------------------------------------------------------------------------------|------------------------|-------|-------------------------|---------|----------------------------|
| on vHIT (affected side) @w6 and @m3                                                            |                        |       |                         |         |                            |
| Body sway until m3                                                                             | All participants       | 92+92 | Unknown                 | Unknown | Mixed models               |
| Enhanced body sway analysis (gait analysis) until m3                                           | Umeå participants only | 25+25 | Unknown                 | Unknown | Mixed models               |
| Total steps since last visit @w6 and @m3.                                                      | All participants       | 92+92 | Unknown                 | Unknown | ANCOVA                     |
| Self-reported vestibular rehabilitation compliance until 6w (mean number of training sessions) | All participants       | 92+92 | Unknown                 | Unknown | Mixed models               |
| Proportion with falls or fractures                                                             | All participants       | 92+92 | Unknown                 | Unknown | Binary logistic regression |
| Proportion with BPPV                                                                           | All participants       | 184   | Estimated frequency 10% | N/A     | Binary logistic regression |

Abbreviations: VSS-SF = vertigo symptom scale short form; EQ-5D = EuroQol five-dimension scale; DHI = dizziness handicap inventory; T25-FW = timed 25-foot walk test; SD = standard deviation; vHIT = video head impulse test; @w6 = at 6 weeks; @m3 = at 3 months; @m12 = at 12 months.

\*Power calculations based on mean gain differences before and after vestibular rehabilitation

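### For VOR gain, ranked ANCOVA cannot deliver the gain difference that Table 2 names and is powered on; for T25-FW and saccades, section 9.3 and Table 2 name different methods

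*Protocol*

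**What the plan says.** Section 9.3 of the protocol states: "Ranked analysis of covariance (ANCOVA) will be used to evaluate intervention effects on T25-FW and VOR gain and saccades". The reason given is that it should be used "as this method provides robust estimates even though there may be extreme outliers in skewed data". Earlier in the same section there is a general rule: "For secondary outcomes with repeated measurements we will use linear mixed models analysis for continuous outcome variables", with logistic mixed models for binary outcomes.

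Table 2, also in section 9.3, then lists a quantity and a method for each analysis:

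- VOR gain: "Between group mean difference of means of vHIT gain (affected side) @w6 and @m3". Method: ranked ANCOVA. Planning values 0.52 (SD 0.24) versus 0.69 (SD 0.25), 50 per arm, power 99%.
- Walking time: "Mean of means T25-FW (seconds) and timed balance tests (seconds) until m3". Method: mixed models.
- Saccades: "Proportion with catch-up saccades" on vHIT. Method: binary logistic regression.

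Section 6.3 describes VOR gain, and how the arms are set against each other, in a third way: "on an aggregated level expressed as the median of VOR means and the changes from baseline at 6 weeks and 3 months will be compared". Section 5.2 makes VOR recovery a superiority objective (objective 3). The synopsis defines the walking endpoint as "The between groups changes in timed 25-foot walk test (time duration; T25-FW) from baseline to 6 weeks and 3 months".

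**The concern.** Ranked ANCOVA replaces the outcome and the baseline value by their ranks and fits the covariance model to those. The treatment coefficient is a difference in adjusted mean ranks. It has no gain unit, it scales with the number of patients ranked, and it cannot be turned back into a difference in gain. The method protects the test against outliers and skew, but it does not estimate the effect on the scale of the endpoint, so the stated reason for choosing it is wrong.

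For VOR gain three descriptions meet on one endpoint: a median summary (section 6.3), a mean difference (Table 2 title and planning values) and a rank test (section 9.3 and the Table 2 method column). The named method yields neither of the first two. Objective 3 could end with a p-value and no adjusted statement of how much gain was recovered, or of what benefit can be excluded if the test is negative.

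For T25-FW and saccades the difficulty is different. Whether a reader gets an interpretable estimate depends on which of two conflicting texts is followed.

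**Working it through.** **1. Where each method is named**

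| Endpoint | Section 9.3 text | Table 2 method | Estimate if Table 2 is followed |
|---|---|---|---|
| VOR gain, 6 weeks and 3 months | Ranked ANCOVA | Ranked ANCOVA | Rank units only |
| T25-FW until 3 months | Ranked ANCOVA | Mixed models | Difference in seconds |
| Catch-up saccades, 6 weeks and 3 months | Ranked ANCOVA | Binary logistic regression | Odds ratio |

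Only VOR gain has ranked ANCOVA in both places. That is two comparisons.

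**2. The plan's own power figure for the gain row**

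Inputs from Table 2: difference 0.69 − 0.52 = 0.17; pooled SD = √((0.24² + 0.25²)/2) = 0.245; 50 per arm, or about 42 after the 15% attrition in the column header (50 × 0.85 = 42.5). Two-sided testing is from section 9.3. Alpha 5% and the pre-post correlation r = 0.6 are from section 9.4, where they are stated for VSS-SF only; carrying r = 0.6 over to gain is an assumption.

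Formula: power = Φ( 0.17 / (0.245 × √(1 − r²) × √(2/n)) − 1.96 ).

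- No covariate (r = 0): n = 50: 0.17/0.0490 = 3.47, power 93.4%. n = 42: 0.17/0.0535 = 3.18, power 88.9%.
- r = 0.6 (SD factor 0.8): n = 50: 0.17/0.0392 = 4.34, power 99.1%. n = 42: 0.17/0.0428 = 3.97, power 97.8%.

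The stated 99% is thus reproduced by an ANCOVA on raw gain with r = 0.6 at 50 per arm. The Table 2 footnote says that the figure rests on gain before and after rehabilitation. A paired calculation at n = 50 gives 98.6% with r = 0.3 and 99.8% with r = 0.5. Either way the figure belongs to a mean difference in gain, not to ranks.

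**3. What ranked ANCOVA returns on such data**

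Simulation: 3,000 runs, normal data, true difference 0.17, SD 0.245, r = 0.6 (assumed).

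| Per arm | Raw ANCOVA: estimate | Raw: power | Ranked ANCOVA: coefficient | Ranked: power |
|---|---|---|---|---|
| 50 | 0.170 | 99.0% | 18.8 ranks | 98.3% |
| 42 | 0.169 | 97.1% | 15.8 ranks | 96.2% |

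The same true difference gives 18.8 or 15.8 depending only on how many patients are ranked. The raw estimate stays at 0.17. The power cost of ranking is about one point (99.0 − 98.3 = 0.7; 97.1 − 96.2 = 0.9).

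**The case against.** **Other endpoints.** A reader might infer from section 9.3 alone that gain, saccades and walking time, each at two visits, all lack an effect size, making six comparisons. The documents do not support that: the Table 2 methods for T25-FW and saccades give a difference in seconds and an odds ratio, and the general rule in section 9.3 also points to mixed models for T25-FW. Section 6.7 compares saccades both as yes/no and as a proportion of impulses, so ranked ANCOVA might be meant for one form and logistic regression for the other; the protocol does not say so. This objection stands, and it limits the missing estimate to gain.

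**Some effect size can be recovered.** The mean-rank difference divided by the total number, plus 0.5, approximates the probability that a patient in one arm has a higher value than a patient in the other: 18.8/100 + 0.5 = 0.69 and 15.8/84 + 0.5 = 0.69. Under normality the planning values imply Φ(0.17/(0.245 × √2)) = 0.69. So it is wrong to say that ranking leaves no effect size at all. But this is neither a mean nor a median difference in gain, and the protocol does not mention it.

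**It could be left to the SAP.** Choosing a companion estimate often is, and section 9.3 does promise crude and adjusted analyses. But here the protocol itself fixes a target quantity, a method and a reason that do not fit together. Table 2 is labelled as an aim-specific analysis plan, and section 9.11 treats this document as outlining the original plan. A later SAP can add an estimate, but the mismatch in the protocol remains.

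**Two further arguments should not be made.** It is tempting to say that ranks are uninformative because a tenfold smaller difference could give the same p-value. If all values shrink tenfold, an ordinary t-test also gives the same p-value. Nor is 0.17 a clean between-arm benchmark, since the footnote describes it as a before-after difference.

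**Conclusion.** The point holds for VOR gain on the affected side, at 6 weeks and 3 months. Both places that name the method prescribe a rank test, described as giving robust estimates, for a row that announces and is powered on a mean difference in gain, while section 6.3 summarises by medians. As written, superiority objective 3 has no specified baseline-adjusted between-arm difference in gain with a confidence interval.

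For T25-FW and saccades the finding is a conflict between section 9.3 and Table 2, not a missing effect size.

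The size is moderate. These are secondary endpoints, and the primary endpoint is already to be reported as an adjusted difference with 95% CI and p-value. Nor do the figures support an inference that ranking leaves the gain comparison underpowered: the simulated cost is about one point. That result rests on normal data and an assumed baseline correlation of 0.6. That the coefficient is in rank units rests on neither assumption.

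**What to change.** 1. In section 9.3, describe ranked ANCOVA as providing a robust test rather than robust estimates. It can stay as the test for VOR gain.
2. For VOR gain, name one baseline-adjusted between-arm difference in gain units with a 95% CI at 6 weeks and 3 months, for example a median difference from quantile regression with a bootstrap interval. Use the same name for it in section 6.3, in section 9.3 and in the title of the Table 2 row. State that the 99% power refers to a mean difference in raw gain, and give the correlation assumed.
3. For T25-FW and saccades, state whether the section 9.3 method or the Table 2 method is the main analysis, and which form of the saccade outcome it covers. Following Table 2 already gives a difference in seconds and an odds ratio, so no extra model is then needed.

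Cost: one additional model for gain at each of two visits, on data already collected, plus wording. The small downside is that a rank-test p-value and a confidence interval from another method may occasionally disagree, so the plan should say in advance which one decides.

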| 9. Investigate the frequency of benign positional paroxysmal vertigo (BPPV) after AVS at different time point and using different evaluation methods; investigate the correlation between BPPV and the DHI, VSS-SF, steps and safety endpoints; and investigate the effect of treatment arm allocation on the risk for BPPV. | 9. The frequency (percentage) of participants with:
BPPV at 3 months after AVS onset; symptoms indicating BPPV 6 weeks after an AVS using a BPPV specific questionnaire;
positional nystagmus (non-BPPV) 3 months after an AVS; positional vertigo (non-BPPV) 3 months after an AVS;
BPPV in the treatment vs control group; and the DHI/VSS-SF/steps/safety results differences between the BPPV, suspected BPPV and non-BPPV groups. |
| Safety objective                                                                                                                                                                                                                                                                                                      | Safety endpoint                                                                                                                                                                                                                                                                                                                                                                                                                          |
| Compare the effects on the risk of falls and fractures and any other of online vestibular rehabilitation compared with standard written instructions.                                                                                                                                                                        | The proportion of participants who has experienced falls/fractures since study start up until 6 weeks, 3 months and 12 months; and the number of falls/fractures in each study arm at the same time points.                                                                                                                                                                                                                                     |

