#### 9.4. Sample size calculation

A change in VSS-SF score of 3 or more has been defined as clinically significant. In an earlier study on a Dutch version of the online vestibular rehabilitation tool on primary care chronic dizziness patients the mean VSS-SF score at three months in the intervention group was 8.1 (SD 7.4), and in the control group 11.5 (SD 9.9). In order to detect a difference in VSS-SF score of 3, assuming a standard deviation of 9 and a correlation between pre and post measurements of 0.6 with 90% power, alpha 5%, we would need n=156 participants, 78 in each arm, using the Shieh sample size calculation method implemented into the Superpower package. Assuming a 15% drop out rate the sample size needs to be increased to n=184 to preserve power. Conservative observational data suggest a yearly incidence of 36 patients with acute onset vertigo and nystagmus per 100,000 inhabitants in the Umeå University uptake area.

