## 9.8. Subgroup analysis

Subgroup analyses will be performed by assessing for interaction by:

- a) baseline diagnostic group (categorical), i.e., unilateral vestibular deficit (most often vestibular neuritis), cerebrovascular vertigo (stroke) and vertigo NOS.
- b) sex (categorical)
- c) age (continuous)
- d) study site (categorical)
- e) baseline symptom severity – VSS-SF (continuous)
- f) BPPV diagnosis or not at 3 months (categorical)

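### The adjusted BPPV arm comparison would rest on about 16 cases for 6 to 8 coefficients; a Firth-penalised fit would remove a moderate exaggeration of the odds ratio and the risk of separated coefficients.

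*Protocol*

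**What the plan says.** Protocol section 9.3 states that crude and adjusted results will both be reported. The adjusted analyses use the baseline value of the outcome and "the prespecified predictors sex, age, level of education, number of chronic diseases and baseline AVS etiology". The sentence names no outcome and excludes none.

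Table 2, in the same section, lists the proportion with BPPV with 184 participants, "Estimated frequency 10"%, power not applicable, and binary logistic regression as the method. Falls or fractures get the same method, with the expected difference and the power given as unknown.

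The arm comparison is a stated aim. Objective 9 in section 5.2 includes to "investigate the effect of treatment arm allocation on the risk for BPPV", and the matching endpoint compares BPPV between treatment and control. Positional testing takes place at 3 months (section 6.3 and Table 1), so attrition applies to it.

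Section 9.8 names three diagnostic groups: unilateral vestibular deficit, "cerebrovascular vertigo (stroke) and vertigo NOS". It gives no shares for them. No section gives an expected number of BPPV cases or says what happens if cases are too few for the adjusted model.

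**The concern.** The protocol fixes three things that do not fit together well: an adjustment set of five predictors, a logistic model, and an event frequency that leaves few cases in a trial of this size.

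Maximum-likelihood logistic regression with very few events per coefficient tends to push estimates away from no effect and widens their spread. It also has no finite estimate for a covariate level that contains no cases, or only cases. An analyst who meets this must drop or merge covariates, or change the method, after seeing the data. Section 9.11 treats relevant departures from the plan in this document as reportable, so such a change may itself become a deviation.

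What is at stake is the reading of one secondary result: whether the adjusted effect of allocation on BPPV, shown beside the crude one, looks somewhat larger and less stable than it should.

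**Working it through.** **Inputs from the protocol.** Evaluable number: "we would need n=156 participants, 78 in each arm". Attrition and total: "Assuming a 15% drop out rate the sample size needs to be increased to n=184 to preserve power" (both section 9.4). BPPV frequency 10% and logistic regression (Table 2). Five predictors (section 9.3). Three diagnostic groups (section 9.8), taken here as the etiology categories. Testing is two-sided: "Two-sided statistical tests will always be performed" (section 9.3).

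**The plan's own figure.** 156 / (1 − 0.15) = 183.5, rounded up to 184. This step reproduces. The point uses only this step and does not depend on how the 156 was reached.

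**Expected cases.** 184 × 0.85 × 0.10 = 15.6. If all 184 are evaluable, 184 × 0.10 = 18.4.

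**Coefficients.** BPPV has no baseline value in Table 1, so that term drops out. Arm, sex, age, education, chronic diseases and etiology at one coefficient each make 6. Three-level etiology makes 7. Three education levels (an assumption, since the protocol does not give them) make 8.

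**Cases per coefficient.**
- 15.6 cases: 15.6 / 6 = 2.6 down to 15.6 / 8 = 1.95.
- 18.4 cases: 18.4 / 6 = 3.1 down to 18.4 / 8 = 2.3.

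**Consequences, by simulation.** There were 1,500 to 2,000 trials per scenario, with 156 participants, 10% BPPV and 7 or 8 coefficients. Covariate distributions and effects, etiology shares and the true odds ratio (OR) are assumptions and were varied. Geometric-mean arm ORs:

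| True OR | Adjusted, maximum likelihood | Crude | Adjusted, Firth |
|---|---|---|---|
| 1 | 0.98–1.06 | near 1 | near 1 |
| 2 | about 2.1–2.3 | 2.0–2.2 | 1.95–2.07 |
| 3 | about 3.4–3.55 | 3.1–3.2 | 2.96–3.04 |

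A true OR of 0.5 gave 0.46–0.48 by maximum likelihood. At a true OR of 2 the exaggeration is 2.1 / 2 = 1.05 to 2.3 / 2 = 1.15, that is 5–15%; part of it is also in the crude OR. Coverage of 95% intervals was 94–97%. The adjusted OR was wrong by more than a factor of two in 25–30% of trials, against 21–26% for the crude OR.

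A further simulation at true ORs of 0.5 and 2 (log OR 0.69 in size) gave:
- maximum likelihood: mean log OR 0.78–0.81 in size, standard deviation about 0.74;
- Firth fit with the same covariates: mean 0.67–0.70, standard deviation 0.62–0.66, and no failed fits.

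The shift is thus about 0.81 − 0.69 = 0.12 at most, or 0.12 / 0.74 = 0.16 of a standard deviation.

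**Separated or non-converging coefficients** (maximum likelihood, 156 participants), by assumed etiology shares:

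| Shares | Trials affected |
|---|---|
| equal thirds | 2–6% |
| 60/20/20 | 10–20% |
| about 75/13/12 | 27–46% |
| 85/10/5 | 55–76% |

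Outside equal thirds, nearly all of these are an etiology group without a BPPV case. The arm coefficient itself could not be estimated in about 0–0.4% of trials at 10% frequency (about 7–8% if the frequency were 5%).

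**The case against.** The strongest reply is that the protocol does not prescribe this model for BPPV by name. The adjustment sentence is general and refers to baseline values that BPPV does not have. The Table 2 row gives one pooled number and no power. A crude comparison will stand beside the adjusted one in any case, and a method for sparse events is commonly left to a statistical analysis plan. The wording of Table 2 does not exclude a penalised fit.

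Much of this stands. The model follows from reading two places together, and the crude comparison limits the damage. But the adjustment sentence excludes no outcome, the arm effect on BPPV is a stated objective, and the method, covariates and frequency are already fixed here. The point is the combination that is fixed, not detail left for later.

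A reader might infer stronger things, which the documents do not support:
- **That the trial would often show a spurious BPPV effect.** There is no bias under no effect, and test size and interval coverage are near nominal. Imprecision is the larger problem.
- **That the model will often fail.** That depends on etiology shares that the protocol does not give. When a fit does fail, it is mostly the etiology term; the arm estimate nearly always survives.
- **That falls and fractures share the problem.** No rate is stated for them, so this holds only if the observed events are similarly few.
- **That the covariates must be cut, or a crude risk difference made the main estimate.** Both are preferences.

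**Conclusion.** The point holds in a limited form. At the protocol's own 10% frequency, the adjusted BPPV arm comparison has about 16 cases (18 without attrition) for 6 to 8 coefficients, about 2 to 3 per coefficient. Ordinary maximum likelihood then exaggerates the arm OR moderately when an effect exists, by about 5–15% at a true OR of 2 or 0.5, and is less precise than it need be. Separated coefficients may occur in anywhere from a few per cent to well over a third of trials, and in more than half at the most uneven mix tried.

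The case count follows from the protocol's figures. The coefficient count also rests on treating the section 9.8 groups as the etiology categories and on the coding of education. The sizes of bias and failure rest on assumed covariate effects and diagnostic shares. The comparison is part of one secondary endpoint with no power claim, and the primary analysis is untouched. This is a cheap improvement, not a flaw that threatens the trial.

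**What to change.** In section 9.3 and the BPPV row of Table 2, state that the adjusted arm comparison for BPPV is fitted by Firth-penalised logistic regression with profile-likelihood intervals, and reported beside the crude comparison already planned. State that the same applies to falls and fractures if the observed events are similarly few.

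Reducing the covariate set is optional. A reduced set that keeps etiology would keep the term that causes most of the separation, and no reduced set was tested here.

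The cost is a sentence of text, slightly less familiar software, and slight shrinkage of the estimate towards no effect. With the full covariate set, the Firth fit failed in at most 0.5% of simulated trials, so a later change of model would rarely be needed.
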